##### Measurements and data collection

De-identified medical records from CHS will be compiled with support from administrators at the two care providers. There are specific variable names in the medical records for questions about exposure to violence, reports of concern to social services, and whether the mother or father had an individual visit with the CHS nurse.

The data that will be retrieved from the CHS medical records are: date for the visit; age of the child; type of contact; information about whether an individual visit has taken place for the parent (yes/no); whether a question on exposure to violence has been asked (yes/no) and the parents’ answer; notes about exposure to violence for the child (yes/no); reports of concern to social services (yes/no); and reason for reports of concern to social services (when a report is made).

Since questions about violence should be asked whenever there is a suspicion of violence, all medical records from the CHS of the two care providers are eligible for inclusion in the data collection. The total number of enrolled children will be used as the denominator when calculating frequencies. Information on FV assessment will be extracted from medical records where documentation of (1) an individual parental consultation, (2) questions about violence or (3) a report of concern is present during the study period.

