Few studies have examined how questions on exposure to violence posed to new fathers in the healthcare settings are working. A few Swedish studies from the CHS context report a lower share of fathers than mothers being asked about violence.^12 13^ To our knowledge, no international studies have investigated how fathers are offered the opportunity to answer questions about their own exposure to violence within a child health or parenting support context.

FV exists in all societies and cultures but there is an increased risk in areas with a higher degree of social vulnerability.^14^ Examining whether parents in areas with different socioeconomic conditions are equally likely to be asked about FV is therefore important. Social vulnerability at a societal level can be measured in several ways. One such measure used within CHS is Care Need Index (CNI), a socioeconomic index used to estimate healthcare needs within an area.^15^ It is based on factors such as single parenthood, unemployment, low educational level and proportion of foreign-born residents in the area. A higher CNI indicates a greater need for support and resources in primary healthcare.

Maintaining routines for asking about violence over time can be difficult, as these practices are often influenced by factors such as workload, staff turnover and access to training. Even routines that are initially well implemented may diminish or become less consistently applied over time.^16^ These organisational factors may also influence healthcare professionals’ confidence in addressing violence, including their preparedness to act when violence is identified. Previous research suggests that a prerequisite for healthcare professionals to ask about exposure to violence is to feel confident about actions and steps to follow if violence is identified.^17^ In Swedish CHS, existing research has focused on the implementation phase of such routines.^12 13 17^ Less is known about how these practices are sustained over time and how nurses experience working with them in everyday clinical practice.

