### Research questions

The specific research questions are:

To what extent are questions about FV posed to mothers and fathers, respectively, in CHS?To what extent is ongoing FV identified among parents that have been asked about it?To what extent have reports of concern been made to social services when FV is identified?To what extent are structural factors (eg, CNI) and organisational conditions (eg, professional education and supervision) associated with nurses’ likelihood of inquiring about FV and responding when FV is identified within CHS?What barriers and facilitators do nurses within CHS perceive when asking about FV?What barriers and facilitators do nurses within CHS perceive in providing support to families affected by identified FV?

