#### Registry-based data from CHS medical records

##### Participants

We will make use of registry data from medical records of children enrolled in the CHS during the period 30 June 2024 to 30 June 2025. Approximately 90 000 children are enrolled in the CHS provided by the two included healthcare providers. The included CHS clinics are based in areas with different socioeconomic characteristics (according to CNI) located in the city, suburbs and surrounding municipalities in the Stockholm region.

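### With all enrolled children as the base, visits never held are mixed with questions not asked, so a CNI association need not reflect nurse behaviour

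*Protocol article*

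**What the plan says.** All places are in the protocol article.

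- **Base for frequencies** (Measurements and data collection): "The total number of enrolled children will be used as the denominator when calculating frequencies". Just before this, "all medical records from the CHS of the two care providers are eligible for inclusion in the data collection".
- **Extraction rule** (same section): "Information on FV assessment will be extracted from medical records where documentation of (1) an individual parental consultation, (2) questions about violence" or a report of concern is present in the study period.
- **Visit status** (same section): whether an individual visit took place is retrieved as yes/no, and the records hold it for mother and father. Child age is retrieved too.
- **Population and window** (Participants): "Approximately 90 000 children are enrolled in the CHS provided by the two included healthcare providers". Records are those of children enrolled "during the period 30 June 2024 to 30 June 2025". The Introduction gives the age range as 0–5 years.
- **Route of the question** (Study setting): the routine question usually comes at an individual visit, for the mother at 6–8 weeks and for the father at 3–5 months. Questions are also to be asked at any time on suspicion.
- **Target** (Research questions, fourth question): the association of structural and organisational factors with nurses' "likelihood of inquiring about FV and responding when FV is identified within CHS".
- **Model** (Analysis, quantitative part): regressions relate questions about violence to CNI and to organisational and clinic-level variables. The regression base is not named.
- **CNI** (Introduction): "It is based on factors such as single parenthood, unemployment, low educational level and proportion of foreign-born residents in the area".

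**The concern.** A parent can be recorded as not asked for three reasons: the child did not pass the routine age in the 12-month window, no individual visit was held with that parent, or a visit was held and the nurse did not ask. Only the third describes what a nurse does at a visit. The enrolled base puts all three into one category, while the fourth research question is worded about nurses.

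The reasons call for different remedies. A gap in visits is met by reaching and offering visits to more parents; a gap at the visit is met by training and support for nurses. The Discussion intends conclusions on equal opportunity by parent gender and area, and on nurses' possibilities to follow the method. The interview clinics are also to be chosen by high and low frequency of asking, so a clinic with low visit uptake could be picked as one where nurses ask little.

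**Working it through.** The article states no visit rate, asking rate, effect size or power, so there is no figure to reproduce. **Every rate below is an assumption**, used to show direction and range.

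**Decomposition.** For one parent, with v = P(visit), q = P(asked | visit) and r = P(asked on indication | no visit):

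P(asked) = v·q + (1 − v)·r

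The odds ratio (OR) compares high-CNI with low-CNI clinics.

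**1. Father availability differs, nurses behave alike.** Let 60% of available fathers be asked everywhere.
- Availability 95% (low CNI): 0.60 × 0.95 = 0.57, odds 0.57/0.43 = 1.326.
- Availability 85% (high CNI): 0.60 × 0.85 = 0.51, odds 1.041, OR = 1.041/1.326 = 0.79.
- Availability 75% (high CNI): 0.60 × 0.75 = 0.45, odds 0.818, OR = 0.818/1.326 = 0.62.

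**2. Visit coverage differs, q = 80% in both groups, r = 0.**
- 60% against 50%: 0.48 against 0.40, OR = (0.40/0.60)/(0.48/0.52) = 0.72.
- 60% against 40%: 0.48 against 0.32, OR = (0.32/0.68)/(0.48/0.52) = 0.51.
- Among visits held, the OR is 1.00 in both cases.

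**3. The mixing can also mask a difference.** Visits 60% against 40%, q = 60% against 90%: 0.60 × 0.60 = 0.36 and 0.40 × 0.90 = 0.36. The OR per child is 1.00; given a visit it is (0.90/0.10)/(0.60/0.40) = 6.0.

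**4. If the regression used only extracted records.** With c = P(report only | no visit, not asked), the extracted share is v + (1 − v)[r + (1 − r)c]. Take visits 60% against 40%, q = 80%, r = 1% against 3%, c = 0.5% against 1%.
- Asked per child: 0.484 against 0.338, OR 0.54.
- Extracted share: 0.606 against 0.424.
- Asked among extracted: 0.484/0.606 = 79.9% against 0.338/0.424 = 79.8%, OR 0.99 from unrounded values.

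With r = 3% against 10% and c = 1% against 2%, the extracted-record OR is 1.05, or 1.15 if q is 60%. An extreme case of 90% against 30% visits, q = 80%, r = 5% and no report-only records gives 72.5% against 27.5% asked per child. Among extracted records it gives 0.725/0.905 = 80.1% against 0.275/0.335 = 82.1%, OR about 1.14. So this set stays close to asking given a visit but loses sight of the access gap.

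**5. Age.** If the 90 000 children form 5 or 6 equal birth cohorts (assumed), 90 000/5 = 18 000 or 90 000/6 = 15 000 pass the routine age in 12 months. An 80% asking rate among them reads as 0.80/5 = 16% or 0.80/6 = 13% of all enrolled. This alone creates no CNI association unless age mix differs by clinic, but the frequency no longer reads as coverage of the routine.

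**The case against.** **The article is a summary.** Covariates, strata and the regression set commonly sit in an analysis plan, which is not shown, and nothing in the article rules out a split by visit. This stands: the lack of a visit term in one paragraph is not the fault. But the enrolled base is fixed here, and it fits poorly with the wording of the fourth research question.

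**The per-child base answers real questions.** The Introduction asks whether parents in different areas are equally likely to be asked. A lower rate because visits do not happen is a true access gap, not an artefact. This also stands: the base should be kept for that question and not used for nurse behaviour.

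**A stronger reading is tempting.** A reader might infer from the extraction rule that the regression sample is selected on its own outcome, since a parent with no visit and no report enters only if asked. The article does not support this. All records are eligible, enrolled children are the denominator, and the rule can be read as collecting numerators. The Data integration section links FV assessment data to clinic variables, which leaves extracted records as a possible regression set, but no sentence says so. Even then the distortion in step 4 is small.

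**The CNI mechanism is not documented.** Single parenthood is one of several area-level components, with no weights given, and the argument is about fathers. The article says that all parents are offered an individual consultation but gives no uptake. A reader might infer that high-CNI clinics must have fewer available fathers; the text makes that plausible, no more.

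**Conclusion.** The concern holds in limited form. If the enrolled base is carried into the CNI and clinic regressions, the result combines visit access, child age and nurse inquiry, and cannot by itself support statements about nurses. Under the assumed rates, identical nurse behaviour gives ORs from 0.79 to 0.51, and a real difference at the visit can vanish. These values illustrate; none is an estimate for this study. The conclusion rests on three things in the article: the enrolled denominator, the tie between the routine question and an individual visit, and the target of the fourth research question. The true size depends on how visit uptake varies with CNI, which the study's own data will show. The change is worth making because the variables it needs are already retrieved.

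**What to change.** - State the base of each regression.
- Among children who reach the routine age in the window, report and model two steps, separately for mothers and fathers: P(individual visit held) and P(asked | visit), each with CNI and clinic predictors.
- Use P(asked | visit) for statements on routine inquiry by nurses under the fourth research question, and the overall per-child rate for the equity question.
- Report indication-based asking outside individual visits separately, with enrolled children as its base, so that this form of inquiry is not lost.
- Show both steps by clinic when interview clinics are chosen.

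**Cost:** one extra model per parent and a smaller, age-eligible denominator. Visit status and child age are already on the retrieval list. The providers may need to supply counts of age-eligible children per clinic whose records meet none of the extraction criteria. Under Study timeline, the register analysis runs to November 2026 and nurses are contacted in January 2027, so the split can be in place before clinics are selected.

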#### Organisational characteristics of CHS clinics

##### Sampling and recruitment

All unit managers and operations managers at the participating CHS clinics will be contacted.

##### Data collection

An electronic questionnaire with questions about organisational characteristics of the included CHS clinics will be distributed via a secure web platform (see online supplemental file 1). The questions cover information on the number of nurses employed, their percentage of full-time employment, years of experience in CHS, number of enrolled children and how many of the nurses that have participated in training about FV. The questionnaire also includes questions on staff turnover in the latest year. It is estimated to take about 15 min to complete the questionnaire. The CNI for each CHS clinic is publicly available and will be retrieved from Region Stockholm.

10.1136/bmjopen-2025-115537.supp1Supplementary data

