##### Data integration

Data from medical records on FV assessment will be linked to corresponding clinic-level variables, including CNI and organisational characteristics, to examine how contextual factors may be associated with assessment practices.

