##### Analysis

Descriptive statistics will be used to calculate the frequency of (1) questions about FV posed to parents, (2) identification of ongoing violence and (3) reports of concern following identification. Differences between mothers and fathers in being asked about violence will be examined using appropriate statistical tests depending on the data distribution. Regression analyses will be conducted to explore associations between questions about violence, CNI and organisational and clinic-level variables. All analyses will be conducted using the statistical software IBM SPSS Statistics for Windows, V.31.0 (IBM).

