### Study timeline

Ethical approval was sought and granted in May 2025. The caregivers were approached and requested for patient and organisational data during October/November 2025. Data management and analysis of the register data was initiated in February 2026 and will be finalised in November 2026. Nurses at selected CHS clinics will be contacted with written information and invitation to participate in interviews in January 2027. Interviews are planned to be conducted in March–June 2027. Data management and analysis of the interview data will be conducted in March–December 2027. The integration of the results of the material from the registry review and the interviews will be compiled and presented in January–June 2028. The timeline of the study is described in online supplemental file 3 table 1.

10.1136/bmjopen-2025-115537.supp3Supplementary data

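### The staff-turnover question looks back over a year that is not tied to the record year, so on the stated timeline it covers only about 58–74% of it

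*Protocol article*

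**What the plan says.** The outcome data are defined under Participants as the records of "children enrolled in the CHS during the period 30 June 2024 to 30 June 2025".

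The organisational data come from an electronic questionnaire to clinic managers. Data collection lists its content: "The questions cover information on the number of nurses employed, their percentage of full-time employment, years of experience in CHS, number of enrolled children", followed by how many nurses have had FV training. No date or period is attached to these items. Turnover is the one item with a stated period: "The questionnaire also includes questions on staff turnover in the latest year".

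The Study timeline gives the only date for this data stream: "The caregivers were approached and requested for patient and organisational data during October/November 2025". It gives no date for completion of the questionnaire.

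The two sources are then joined. Data integration states: "Data from medical records on FV assessment will be linked to corresponding clinic-level variables, including CNI and organisational characteristics". Analysis adds: "Regression analyses will be conducted to explore associations between questions about violence, CNI and organisational and clinic-level variables". Together these serve the fourth research question, on whether structural factors and organisational conditions are associated with asking about FV and responding to it.

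**The concern.** The record window is fixed in the calendar. The turnover period is relative and moves with the day on which each manager answers. Because the request went out after the record window had closed, a look-back from that point misses the first months of the outcome year and adds months in which no outcome was recorded. Managers who answer at different times would also report on different periods.

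The undated items carry a related risk. If they are answered as at completion, the training count would include nurses trained after June 2025 and leave out trained nurses who worked during the window but have since left. Staffing and experience would shift in the same way.

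What is at stake is the accuracy of the clinic-level exposures in the regression. The Introduction itself names staff turnover and access to training among the influences on whether routines for asking are kept up, so the protocol expects these variables to matter. Misdating them would generally blur real associations. The large number of records does not help, because the error sits in the clinic-level exposure. Once the answers are in, analysis cannot recover the right period.

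**Working it through.** The article states no figure for the overlap, so there is none to reproduce. The check is calendar arithmetic.

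**Inputs from the article**
- Outcome window: 30 June 2024 to 30 June 2025, which is 366 days counted inclusively (Participants).
- Request for organisational data: October/November 2025 (Study timeline).
- Turnover period: the most recent year, with no calendar anchor (Data collection).

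**Assumptions**
- The most recent year means the 12 months (365 days) ending on the day of completion.
- Completion fell within the stated request period. The article dates the request, not the completion.

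**Formulas**
- Overlap = days from the start of the look-back to 30 June 2025, inclusive.
- Coverage = overlap / 366.
- Days after close = completion date − 30 June 2025.
- Days missed at the start = 366 − overlap.

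| Completed | Look-back starts | Overlap (days) | Coverage | Missed at start (days) | After close (days) |
|---|---|---|---|---|---|
| 1 Oct 2025 | 2 Oct 2024 | 272 | 272/366 = 74% | 94 | 93 (3.1 months) |
| 31 Oct 2025 | 1 Nov 2024 | 242 | 242/366 = 66% | 124 | 123 (4.0 months) |
| 30 Nov 2025 | 1 Dec 2024 | 212 | 212/366 = 58% | 154 | 153 (5.0 months) |

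On the stated timeline, then, roughly 3 to 5 months at the start of the outcome year are not covered, and 3 to 5 months after its end are included.

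**Sensitivity to the assumptions**
- Later completion (assumed dates, not stated in the article): 1 February 2026 gives 149 days (41%), 28 February 2026 gives 122 days (33%), and 30 June 2026 or later gives 0.
- If managers read the item as a calendar year: 2024 gives 185 days (51%) and 2025 gives 181 days (49%).
- If the item named the record window explicitly: 366/366 days (100%).

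No such calculation is possible for staffing, experience and training, because the article gives them no reference date.

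**The case against.** The strongest reply is that the article only summarises the questionnaire. The instrument is in supplemental file 1, which is not shown, and reference dates for individual items belong there. This stands for staffing, experience, enrolment and training: the article does not say that they are asked as at completion, so a mismatch there is a possibility only. It carries less weight for turnover, where the article does state a period and that period is relative.

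Several stronger readings are tempting, and the documents do not support them:
- *The exposures come from a different year and do not describe the clinics that produced the outcomes.* The clinics are the same, and on the stated timeline the turnover year is shifted by 3 to 5 months and still shares 58% to 74% of the window. Staffing a few months later is an imperfect proxy, not an unrelated measure.
- *The overlap may be nil.* That needs completion at the end of June 2026 or later, which the article does not state. The future tense used for distributing the questionnaire is weak evidence of late completion, since the article also uses it for register analyses that its timeline says have begun.
- *The time order needed for the fourth research question is broken.* That question, and the analysis text, concern association. Time order is blurred, but the question is not defeated.
- *The training association could reverse.* This would need training to have been directed at low-asking clinics after June 2025, and nothing in the article says so. Training and experience are also cumulative, so a delay of some months adds only what accrued in those months.
- *The managers' enrolment count will distort the frequencies.* Measurements and data collection sets total enrolled children as the denominator within the section on record data. Nothing says that the managers' count replaces it.

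**Conclusion.** The concern holds in a limited form. As described, the turnover item is not aligned with the record year. If it means the 12 months before completion, and completion was in October/November 2025, it covers about 58% to 74% of the outcome year and includes 3 to 5 months after it closed. Later completion would lower the coverage. For staffing, experience and FV training the article leaves the reference date open, so answers may also reflect changes after the window unless the supplemental questionnaire dates them.

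The consequence is possible misclassification of clinic-level exposures and blurred associations in the regression for the fourth research question. The descriptive frequencies taken from the records do not depend on it. Confidence is good for turnover, where the wording is explicit, and moderate for the undated items. The point is worth correcting because it is cheap to correct and cannot be repaired at analysis.

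**What to change.** Tie the questionnaire to the record window:
- Ask for turnover from 30 June 2024 to 30 June 2025, with the dates written into the item.
- Ask for number of nurses, full-time percentage and experience for that same period. A single snapshot at its first day would miss nurses hired during the year who did some of the asking.
- Count nurses trained in FV by a stated date within or before the window, and record the year of training.
- Take enrolled-children counts from the register for the same period wherever clinic size enters an analysis.

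If supplemental file 1 already sets these dates, it is enough to say so in the article. If the questionnaires have already gone out, send managers a short follow-up on turnover in the window and on training dates. Failing that, report the mismatch and its likely extent as a limitation.

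The cost is rewording a form that takes about 15 minutes, or one brief further contact. The downside is some recall burden for managers and, because participation is voluntary, possible non-response to a follow-up.
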